## Abstract

**Background:**

Externalising and internalising problems affect one in seven school-aged children and are the single strongest predictor of mental health problems into early adolescence. As the burden of mental health problems persists globally, childhood prevention of mental health problems is paramount. Prevention can be offered to all children (universal) or to children at risk of developing mental health problems (targeted). The relative effectiveness and costs of a targeted only versus combined universal and targeted approach are unknown. This study aims to determine the effectiveness, costs and uptake of two approaches to early childhood prevention of mental health problems ie: a Combined universal-targeted approach, versus a Targeted only approach, in comparison to current primary care services (Usual care).

**Methods/design:**

Three armed, population-level cluster randomised trial (2010–2014) within the universal, well child Maternal Child Health system, attended by more than 80% of families in Victoria, Australia at infant age eight months.

Participants were families of eight month old children from nine participating local government areas. Randomised to one of three groups: Combined, Targeted or Usual care.

The interventions comprises (a) the Combined universal and targeted program where all families are offered the universal *Toddlers Without Tears* group parenting program followed by the targeted *Family Check-Up* one-on-one program or (b) the Targeted *Family Check-Up* program. The *Family Check-Up* program is only offered to children at risk of behavioural problems.

Participants will be analysed according to the trial arm to which they were randomised, using logistic and linear regression models to compare primary and secondary outcomes. An economic evaluation (cost consequences analysis) will compare incremental costs to all incremental outcomes from a societal perspective.

**Discussion:**

This trial will inform public health policy by making recommendations about the effectiveness and cost-effectiveness of these early prevention programs. If effective prevention programs can be implemented at the population level, the growing burden of mental health problems could be curbed.

**Trial registration:**

ISRCTN61137690

## Background

Mental health problems account for a substantial burden of disease globally, with the World Health Organisation predicting that by 2030, mental health problems will be the highest ranking disease in terms of burden in affluent countries [1]. Similar to Australian adults (where up to one in five have a mental health problem) [2], one in seven Australian children (aged 4–17) has a mental health problem, yet in a national survey only a quarter of children accessed treatment [3]. The relative lack of child and adolescent mental health services poses a pressing problem as prevalence persists [1]. To curb and manage this problem, effective prevention is essential.

During childhood, mental health problems most commonly manifest as externalising (behavioural) and internalising (emotional) problems [4-8]. Externalising problems include conduct disorders, oppositional defiance and aggression, while internalising problems include anxiety, social withdrawal and depression. These problems bear considerable ongoing costs for individuals, families and society [9] including difficulties with peer interaction, learning, family stress and the need for clinical services [10]. Associated problems can also be enduring; mental health problems in early childhood are the single strongest longitudinal predictor of mental health throughout childhood and into early adolescence [4]. If left untreated, up to 50% of these problems can persist throughout childhood and then adolescence [6], resulting in an increased risk of school dropout, substance abuse, family violence, unemployment, involvement with criminal justice services, and suicide [9,11].

Externalising and internalising problems share early risk factors, many of which are identifiable in the pre-school years [7,12]. Risk factors include family stressors such as parental mental health problems, single parenthood, substance abuse, relationship conflict, social isolation, low income and maternal perception of difficult child temperament [7,12]. The single strongest modifiable risk factor, however, is negative parenting practices [13,14]. Negative parenting practices characterised by harsh discipline and low warmth are predictive of externalising problems, and over-involved protective parenting and low warmth are predictive of internalising problems [12,15]. Thus, a focus on parenting practices is an essential component of prevention programs for mental health problems in childhood.

### Universal and targeted approaches to prevention of child mental health problems

Two broad types of prevention programs exist: universal (i.e. provided to all) and selective or targeted (i.e. provided to ‘at risk’ populations), but in reality the boundaries between these two approaches are often blurred [16]. Our systematic review of randomised controlled trials of early intervention and prevention programs for child mental health revealed a number of targeted programs that reduced externalising problems in randomised controlled trials [17]. These include the Olds Home Visiting Program (an intensive program promoting maternal health and a good parent-infant relationship in the first two years of life) that has shown lasting reductions in anti-social adolescent behaviour [18], yet lacks demonstrated comparable efficacy when translated to the Australian population [19,20]. Similarly, *The Incredible Years* program has shown reductions in externalising behaviours [17] and more recently has shown promise for reducing co-occurring internalising problems in children aged 4–7 years with existing oppositional defiant disorder [21]. However, both of these programs are limited by their resource intensity with a minimum of 40 contact hours per family [17,21]. The most promising targeted program, in terms its brevity and effectiveness, is the *Family Check-Up* program (detailed below in Methods). The *Family Check-Up* provides a relatively small number of one-on-one sessions (an average of 3.3 sessions per family) to ‘at-risk’ families i.e. those experiencing child behaviour problems and/or economic and family hardship. It has proven effective in preventing both externalising and internalising problems [22]. However, it has only been trialed in disadvantaged American families. Yet child mental health problems occur across all socioeconomic groups and numerically the bulk of problems occurs in middle and high socioeconomic groups in many countries, because these groups comprise the bulk of society [17,23]. There is a need, therefore, to test the efficacy of the *Family Check-Up* in countries other than the US, across a range of socioeconomic groups.

Although often effective, targeted programs can be stigmatising for families and lead to poor uptake rates, as low as 20% in some studies [23]. An alternative approach to improve the reach of targeted programs may be to offer a universal prevention program first. Universal programs include *Triple P* (i.e. Positive Parenting Program) which has been trialed in both Australia [24] and Germany [25]. In these two trials, *Triple P* involved four weekly 2-hour parenting groups plus optional 15-minute phone contacts for parents of children aged 3–6 years. Improvements in parenting, child behaviour and family stress have been reported [24,25]. Neither trial however, delivered *Triple P* in a truly universal manner [24,25]. The recruitment rate for the German trial was 31% of the population and a high proportion of these children (32%) had pre-existing behaviour problems [25]. The Australian trial was restricted to families from low socioeconomic areas, was not randomised and nearly half of the children had pre-existing behaviour problems. Population recruitment rates need to be higher in universal prevention trials for generalisability, interpretation of effect sizes and understanding the logistics of program dissemination [24].

The *Toddlers Without Tears* program is one of the few truly universal mental health prevention programs [15,26,27]. Developed in Australia to address negative parenting styles that can contribute to child mental health problems, it consists of a nurse delivered one-on-one session at child aged 8 months followed by two parent group sessions delivered at child age 12 and 15 months by maternal and child health nurses and a co-facilitator with expertise in parenting. In a large (N = 733) randomised controlled trial with high recruitment (69% of the population), the program led to some modest improvements in parenting practices but did not prevent behavioural and emotional problems in preschoolers [26,27]. This suggests that this program alone is insufficient to prevent child mental health problems. Whether this program combined with a targeted program could lead to greater population reach, uptake and effectiveness remains to be determined. Given that no trial to date has evaluated the effects of a combined universal-targeted approach versus a targeted approach alone, this trial’s findings are likely to be of international significance.

The *Families in Mind* trial therefore aims to compare the effectiveness, cost-effectiveness and population reach and uptake of a targeted approach alone (the *Family Check-Up* program) with a combined universal (the *Toddlers Without Tears* group parenting sessions) and targeted approach in the Australian population. Both programs will be delivered through existing child health workforces in the state of Victoria, and will be compared to the provision of usual care alone (‘control’ group).

We hypothesise that families offered this targeted program, either alone or in combination with this universal program, will have better outcomes than families who are not offered these programs. Outcomes include mean scores at child age three, four and five years for:

a) child externalising and internalising behaviour problem s (primary outcome)

b) harsh discipline and nuturing parenting practices (primary outcome), and

c) parental mental health (secondary outcome)

Additionally, we hypothesise that uptake of the targeted program by ‘at risk’ families will be greater with the combined approach where the universal parenting program precedes the targeted program (to reduce stigma), than with the targeted program alone.

## Methods/design

Figure 1 summarises the components of the trial and their timing. It graphs each stage of all three arms of the trial, in the manner suggested by Perera et al. [28]. The trial is registered with an international trial registry (ISRCTN61137690) and will be reported in accordance with the CONSORT statement [29].

**Figure 1 F1:**
[figure not shown]
Graphical depiction of components of the trial.

### Design

Three-arm cluster randomised controlled trial comprising Arm A (combined approach of *Toddlers Without Tears* program followed by the *Family Check-Up* program); Arm B (*Family Check-Up* program only); and Arm C (Usual care) (see Figure 1). The trial runs from 2010 to 2014.

### Recruitment process

To develop the sampling frame, the 31 local government areas (LGAs) comprising greater Melbourne (population 3,592,591 in 2006), Australia, were first ranked according to the mean score of all inhabitants on the census-based Socio-Economic Indexes for Areas (SEIFA) index of relative disadvantage [30], and then divided into tertiles. A convenience sample of three local government areas from each of the low, middle and high tertiles was then approached to take part in the trial.

Maternal and child health (MCH) nurses in these areas then consecutively invited families attending their routine 8-month well-child visit over a five-month period (Aug10-Dec10) to learn more about the study. The MCH service is a universal primary health service available free to families in every local government area in Victoria. It provides ten ‘Key Ages and Stages’ visits with an MCH nurse from birth to school entry, with 84% attendance at the 8-month MCH visit [31]. Nurses passed interested families’ contact details on to the research team, who then contacted the family by phone. Families who did not attend their scheduled 8-month visit were sent a letter inviting them to contact the research team for more information about the study.

During the recruitment call, the research team provided background information and a description of the programs being trialed. Families interested in participating were sent an enrolment pack containing the participant information statement, consent form and the 8-month intake survey. Participants enrolled when a signed consent form and an intake questionnaire were returned by post.

### Inclusion criteria

As this is a population-level effectiveness trial for programs delivered in a community setting, inclusion criteria were as broad as possible: all 8-month old babies who attended or planned to attend their MCH service in the participating local government areas between August 2010 and December 2010.

### Exclusion criteria

Parents with insufficient spoken English to participate in parenting programs were excluded. This was determined by the referring nurse or the research team at the recruitment phone call. Infants with major medical diagnoses were also excluded.

### Allocation

MCH centres (n = 133) were grouped into clusters (n = 85) before randomisation to avoid cross-contamination of new intervention program skills, which could have occurred when a nurse worked across multiple centres - had these centres not been allocated to the same trial arm. Randomisation of clusters was stratified by LGA. Clusters were rank-ordered within LGA according to the number of participants recruited and block randomisation was used with fixed block sizes of three to minimise the imbalance in the number of participants in each of the three trial arms. Randomisation was performed after the recruitment phase by a statistician independent of the recruitment process. Families and nurses were notified of their group allocation in writing.

### Interventions

#### Content

The universal program is a revised version of the *Toddlers Without Tears* program that incorporates feedback from the previous trial [26,27]. Based on parent feedback, the group sessions are extended (to include strategies around prevention of internalising behaviours) and delivered around child age 15, 18 and 24 months (rather than the original 12 and 15 months), as this better matches the toddler period when most children become mobile and more challenging in their behaviours. The information covered in these three group sessions provides evidence-based guidance on developmental expectations of toddler behaviour, strategies to encourage desirable behaviours (e.g. praise and rewards) and strategies to manage problematic behaviours (e.g. ignoring, logical consequences, distraction, quiet time and anxiety desensitization) [27].

The *Family Check-Up*[22] is a one-on-one family support program consisting of in-home sessions with a ‘parent consultant’ – a trained psychologist. The *Family Check-Up* aims to address problems in the family environment known to impact on children’s behavioural and emotional development [22]. The *Family Check-Up* will be offered to families in the Combined and Targeted groups with toddlers identified as ‘at risk’. Children will be deemed at risk if they score over one standard deviation above the normative mean at child age two years for a) externalising problem behaviour scores on the Child Behavior Checklist (CBCL) [32] and/or b) the Inhibitory Control subscale on the Children’s Behavior Questionnaire and/or c) the Harsh Discipline subscale on the Parent Behavior Checklist [14]. Families that accept will then be visited by a parent consultant specifically trained in the program, who will follow Shaw, Dishion and colleagues’ procedure for profiling family strengths and difficulties by motivational interviewing assessment/intervention. The *Family Check-Up* consists of an initial ‘Get to Know You’ session with the child’s primary caregiver/s which includes an interview and observational assessment task. At this session, the parent consultant will ask families for written consent to (1) use their questionnaire data for family profiling, and (2) video record some parent–child interactions. During the second ‘Feedback’ session, the parent consultant presents detailed integrated assessment results of child and family strengths and difficulties on a clear visual Child and Family Profile [33]. If the toddler is ‘at risk’ of developing behaviour and/or emotional problems on the Child and Family Profile, families will be offered up to four further ‘Intervention’ sessions focusing primarily on parenting skills and related family stressors, with referrals to appropriate services in the community for additional support as required (e.g. housing support, drug and alcohol advice).

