### Process: combined arm

The first program of the Combined arm will be *Toddlers Without Tears,* the series of three parenting group sessions running for approximately 2 hours each, offered to all families randomised to this arm. An MCH nurse and psychologist with experience in facilitating parenting groups will deliver each session to groups of 4–12 parents. The sessions involve role plays with practice activities, multi-choice scenario discussions, parent education activities utilising parent hand outs, and summarising ideas to practice at home directly with toddlers. All sessions are supported by *Toddler without Tears* parent handouts. Parents who do not attend a session are mailed the relevant parent handouts and offered a 30 minute telephone consultation with a psychologist to discuss the key messages provided in the group session and handouts.

Families in this Combined arm group that are identified with a child ‘at risk’ at age two years will be offered the *Family Check-Up.* We estimate that ≈ 10% of families will be eligible for the *Family Check-Up*; these families will receive a phone call from the research team inviting them to participate in the *Family Check-Up* program. Families will be free to accept or decline this offer.

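### The at-risk rule uses one upper-tail cut-off for three scales; for Inhibitory Control, read plainly, that flags high-control toddlers, and no scoring direction is given

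*Protocol article*

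**What the plan says.** The rule is in the protocol article, Interventions, Content: "Children will be deemed at risk if they score over one standard deviation above the normative mean at child age two years". That one condition governs a list joined by and/or. The list starts with "externalising problem behaviour scores on the Child Behavior Checklist (CBCL) [32] and/or b) the Inhibitory Control subscale" of the Children's Behavior Questionnaire and ends with the Harsh Discipline subscale of the parenting checklist. No separate direction is given for any item. The Inhibitory Control subscale is named nowhere else in the article, and reverse scoring is not mentioned.

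The rule has two uses:

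- **Offer of treatment.** It decides who is offered the Family Check-Up in the Combined arm and, by the same criteria, in the Targeted arm (Process: targeted arm). The abstract (Methods/design) says that this "program is only offered to children at risk of behavioural problems".
- **Denominator for uptake.** The hypotheses that close the Background state that uptake by at-risk "families will be greater with the combined approach where the universal parenting program precedes the targeted program". Analyses tests this among at-risk families with a marginal logistic model.

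On the expected size of the group, Process: combined arm estimates that about "10% of families will be eligible for the" programme.

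**The concern.** A single upper-tail cut-off suits scales on which a high score is adverse. It suits externalising problem scores and harsh discipline. Inhibitory control is, by its name, a capacity, so a high score would ordinarily mean more of it. Followed literally, the second criterion then brings in toddlers with high control and passes over those with low control, which is hard to square with a programme meant for children at risk of behavioural problems.

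Two things depend on it. Families in both active arms could be offered in-home sessions with a psychologist because their toddler is well controlled, while some intended families receive no offer. The uptake comparison would then be made in a group that is partly not the one the hypothesis describes. Anyone who applies the published rule elsewhere, as the trial's policy aim invites, would inherit the same reading.

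**Working it through.** This is mainly a check of wording and logic; arithmetic serves only to show the size of the group.

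**1. Direction, scale by scale** (Interventions, Content)

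| Criterion | What the name describes | Tail the rule selects | Fits the target? |
|---|---|---|---|
| (a) CBCL externalising | problem behaviour | above +1 SD | yes |
| (b) Inhibitory Control | a capacity | above +1 SD | no, on the plain meaning |
| (c) Harsh Discipline | an adverse practice | above +1 SD | yes |

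**2. What (b) does under each possible scoring**

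| Scoring of (b) | High-control toddler | Low-control toddler |
|---|---|---|
| High score = more control | flagged | flagged only through (a) or (c) |
| Reversed, high score = less control | not flagged by (b) | flagged |

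The article does not say which row applies. The wording fits the target only in the second.

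**3. Can the eligibility estimate settle the direction?** Assume normal scores and a sample at the norm.

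- One scale, upper tail: P(Z > 1) = 0.1587. Lower tail: P(Z < -1) = 0.1587. Criterion (b) alone flags 15.9% whichever tail is meant.
- Any of three criteria: at least 15.9% (complete overlap) and at most 3 x 0.1587 = 47.6% (no overlap), again for either tail.

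The plan's figure of about 10% lies below both ranges, so it does not show which tail was intended.

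**4. Size of the at-risk group**

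- Inputs: 492 recruited per arm and 20% attrition by age five (Power calculation and study population); about 10% eligible (Process: combined arm).
- 0.10 x 492 = 49.2, about 49 families per active arm; 2 x 49.2 = 98.4, about 98 in both.
- If all the attrition fell before age two (an assumed extreme): 492 x 0.8 = 393.6, and 0.10 x 393.6 = 39.4, about 39 per arm.

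These figures describe the group in which a misdirected criterion would act. They do not measure how many children are misdirected. That number would need the scoring direction and the correlations among the three scales, and the article gives neither.

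**The case against.** The strongest reply is that the cut-off applies to a score, and the article does not say what a high score on this subscale means. Scoring is commonly left to a manual, a full protocol or an analysis plan. If the trial scores the subscale so that high means difficulty, the sentence is correct for the score used and merely incomplete. This stands: the operational error is conditional, and the absence of scoring detail is not in itself a fault. What remains is that the article does state a direction, gives it to all three scales alike, and names one of them for the opposite quality. That is a stated eligibility threshold which a reader would apply the wrong way round.

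It can also be said that the programme addresses emotional as well as behavioural development, so high control might have been meant as a marker of emotional risk. The article gives no such rationale for the screen, the abstract names behavioural problems, and low-control toddlers would still be missed on (b). The mention of children at risk "of developing behaviour and/or emotional problems on the Child and Family Profile" concerns a later step, after the offer is accepted. That step can keep wrongly flagged families out of the further sessions, but it cannot recover children who were never flagged.

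The Background's description of Family Check-Up families as "those experiencing child behaviour problems and/or economic and family hardship" should not be used against the rule. It describes the existing programme, not this trial's eligibility.

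A reader might infer three stronger conclusions, and the documents support none of them:

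- **The trial screened the wrong children.** This needs the scoring direction, which is not given.
- **The uptake comparison is biased between arms.** The same criteria apply in both arms, so this point gives no ground for that.
- **The primary comparison is compromised.** Analyses includes all families that provide outcome data, by randomised arm, whether or not they were flagged.

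**Conclusion.** The point holds as a defect in a stated eligibility rule, with a conditional operational consequence. Read plainly, criterion (b) selects toddlers with high inhibitory control and does not flag those with low control unless they meet (a) or (c), contrary to the abstract's target. This rests on the plain meaning of the subscale's name.

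- **If the score is not reversed**, the offer of the Family Check-Up in both active arms, and the at-risk denominator for uptake, partly concern the wrong children.
- **If the score is reversed**, the operational effect is zero and only the text needs completing.

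The number affected cannot be derived. It would arise around a planned at-risk group of about 39 to 49 families per active arm. The text should be corrected in either case, because the rule as printed cannot be applied safely without knowing the scoring.

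**What to change.** State the cut-off by scale: more than 1 SD above the normative mean for CBCL externalising and for Harsh Discipline, and more than 1 SD below it for Inhibitory Control (or more than 1 SD above it on an explicitly reverse-scored version). Then check that the screening algorithm and the denominator of the uptake comparison both use that definition.

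The cost is one sentence in the eligibility rule and one check of the scoring program. Sample size, visits and instruments do not change.
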